### Sampling approach and recruitment

The population for the study will be individuals attending mosques and Muslim community groups in Luton and Peterborough. We will target mosques that are in catchment areas of GP practices with low bowel cancer screening uptake. The process for identifying potential mosques to participate in the study is outlined in S1 Appendix. Discussions with community leaders will take place to identify which mosques would be best placed to deliver the intervention, and which mosques would be best to support recruitment of participants for the comparison group. Whilst there are limitations to this, and the potential to introduce bias, the intervention is based on the model that the clinicians deliver the intervention within their communities. As a feasibility study, it will also be helpful to work with the mosques and communities who are willing to engage.

Gender specific sessions will be planned in consultation with community leaders, clinicians and patient public involvement representatives to ensure that both men and women are able to participate in the study. As a minimum in both Luton and Peterborough, we plan to work with one mosque for men and one community group for the women in the intervention group plus two mosques/two community groups for the comparison group.

Representatives of those who are eligible for the study are being recruited to ensure that those who rely on family support can participate. Some of those who are eligible may prefer to ask a representative to attend the session rather than attend themselves, due to language or other barriers.

Strategies and approaches to promote the study and to support recruitment of participants for the intervention and comparison groups, will be agreed in consultation with the project advisory group and the patient public involvement (PPI) representatives. These are likely to include 1) information provided at prayer sessions by the Imam (or community group meetings by the group leader); 2) using social media to share links to written information as well as short, pre-recorded video clips in appropriate languages, 3) local radio, 4) printed material in relevant languages, and 5) case studies. We will also engage with key stakeholders e.g. local pharmacists, schools (e.g. family workers), local councillors, women’s groups, and GP practices to raise awareness of the study.

Clinicians to deliver the intervention will be recruited through the BIMA volunteer network which has over 6,000 members who are professionally vetted and are trained to deliver the presentation and anticipate questions. These professionals are themselves part of the target communities. Individual participants will be recruited through Muslim community/faith groups in the target areas identified, using purposive and opportunistic sampling and recruitment methods, with community leaders and clinicians within the communities promoting the sessions.

Peer-researchers with competence in at least two of the relevant languages (Urdu and Bengali) identified through the mosques will be trained to support the completion of consent forms and study surveys. They will also be trained to support the facilitation of the focus groups. We anticipate that this will avoid the potential situation of lack of trust or openness that may arise if non-Muslim researchers are leading the focus group discussions. Once identified, the research team will hold a virtual training session with the peer-researchers. The training will include an overview of the study, the role of the peer-researchers, with a particular focus on the completion of the consent form and the baseline and post intervention surveys, how to conduct the focus group. Anticipated challenges, and how to overcome them, will also be discussed.

Given the exploratory nature of this study, it was thought that a non-randomised approach would be operationally more practical. Sites will be identified opportunistically, which did not lend itself to randomised design. As this is not a randomised study, participants will be able to choose to be part of the comparison group if they attend a venue which is acting as an intervention site and prefer not to access the intervention, and participants who attend a venue which is acting as a comparison group site will be able to complete the intervention if they wish to receive the intervention. Data analysis will be carried out on individual responses. Given the planned sample size it will be difficult to investigate outcomes by ethnic group within the Muslim population.

To encourage participation in both the intervention and the study groups in this study, we propose to make a monetary donation of five hundred pounds to each participating mosque. Given the limited study budget it will not be possible to provide individual incentives.

One intervention session will be delivered at each intervention site as part of the feasibility study. Part of the feasibility study will be to assess how many participants attend the session as a result of the promotion as outlined above.

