### Inclusion and exclusion criteria

#### Intervention and comparison groups

Inclusion criteria.

Individuals aged 56 years and over (in line with the National Bowel Cancer Screening Programme eligibility, 56 was the minimum age for inclusion in the screening programme at the time of protocol development) [30]Individuals aged under 56 years participating on behalf of a friend/relative/someone they provide care for who is aged 56 years and over. The justification for this is that a member of the Mosque or Muslim community may be living with or caring for someone who is eligible for bowel cancer screening, and so can attend on their behalf. The surveys will capture whether they are responding on behalf of someone elseUse of English as a first languageUse of another language (including Bengali and Urdu) if translation support is available

Participants who require support with translation will be encouraged to ask family members where possible; alternatively, community volunteers will also be available to support participants with the completion of the relevant surveys.

*Exclusion criteria*.

Individuals with a recent bowel cancer diagnosis and/or currently undergoing treatmentAged under 56 years old (if not representing an individual who meets the eligibility criteria)Use of a language for which support from family members and/or community volunteers cannot be found

Feasibility studies do not include formal sample size calculation [31]. As a feasibility study, a sample of 250 participants will be obtained consisting of 100 in the intervention group and 150 in the comparison group. As well as being a pragmatic sample size, this will provide a 95% confidence interval for the proportion of participants in the intervention group who request and/or complete and return a bowel screening kit to an accuracy of ±0.1 and for the participants in the comparison group to an accuracy of ±0.08. Recruitment rates and baseline to 6-month follow-up percentage attrition will be estimated for the two groups. The effects sizes for the differences in proportions between the two groups will give an estimate of the sample sizes required in a future definitive study.

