## Data analysis plan

### Phase 1: Outcome evaluation

Analysis will be undertaken comparing responses between the intervention group and the comparison group using SPSS. As the primary focus in a feasibility study is on the methods for dealing with the feasibility objectives rather than statistical testing [31] results will be presented using descriptive statistics (e.g., mean, proportion) and associated 95% confidence intervals. In addition, to gain further insight into an appropriate sample size for a definitive study, exploratory univariate statistical analyses (e.g., t-tests, chi-squared test) will be performed. At baseline we will compare demographic data and eligibility for bowel screening to determine differences in baseline characteristics between the intervention and comparison groups. This will inform our interpretation of any differences in outcomes and enable us to identify demographic and eligibility differences in those who chose to take up the intervention compared to those who did not. Likert Scale responses to questions assessing knowledge, attitudes and intention to take up screening will be gathered at baseline (both groups), post-intervention (intervention group only) and at 6-month follow-up (both groups). This will enable us to compare understanding of screening between groups at baseline and 6-month follow-up, and, for the intervention group, short-term changes in understanding following the intervention.

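### The stated ±0.1 and ±0.08, and the individual-level intervals and tests, assume independent participants, although recruitment and delivery are clustered in a small number of venues

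*Protocol article*

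**What the plan says.** All references are to the protocol article; no separate analysis plan is shown.

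- **Sample size and precision** (Participants and sample size, Intervention and comparison groups): "a sample of 250 participants will be obtained consisting of 100 in the intervention group and 150 in the comparison group". The size is called pragmatic, and the resulting 95% intervals are said to estimate the proportion requesting or returning a kit "to an accuracy of ±0.1 and for the participants in the comparison group to an accuracy of ±0.08". The same paragraph carries the between-group effect sizes forward to the planning of a definitive study.
- **Sites** (Sampling approach and recruitment): as a minimum in each of the two towns, "we plan to work with one mosque for men and one community group for the women in the intervention group", with two mosques and two community groups for comparison.
- **Delivery** (same section): "One intervention session will be delivered at each intervention site as part of the feasibility study". The section The intervention describes a one-hour teaching session given to a group, in single-sex groups, with a virtual alternative.
- **Unit of analysis** (Sampling approach and recruitment): "Data analysis will be carried out on individual responses". This follows directly on the statement that people at either kind of venue may choose the other group.
- **Methods** (Data analysis plan, Phase 1): descriptive summaries with 95% intervals, and "exploratory univariate statistical analyses (e.g., t-tests, chi-squared test) will be performed".

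The article nowhere mentions clustering, a design effect or an ICC.

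**The concern.** People recruited at one venue share a town, a congregation or community group and usually a sex. In the intervention group they also share a session, its presentation and its questions and answers. The article targets mosques by the screening uptake of local GP practices, and its own regional audit found that uptake varied with practice-level deprivation and ethnicity. Some positive correlation in uptake within venues is therefore to be expected.

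An interval or test that treats such people as independent overstates the information in the sample. Two things are at stake. The precision offered as support for the sample size would not be delivered. And a later study delivered by venue would lack the design effect it needs, because this study does not plan to estimate the between-venue variation.

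**Working it through.** **Inputs from the article.** n = 100 and 150; 95% intervals; stated half-widths 0.1 and 0.08; a minimum of one mosque and one community group per town for intervention, so 2 × 2 = 4 sites. Comparison sites: 2 × 4 = 8 if the sentence is read per town, or 4 in total on another reading.

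**Assumptions.** The article does not state the proportion; p = 0.5 is the worst case. It gives no ICC; 0.01, 0.02 and 0.05 are used for illustration. Sites within a group are taken as equal in size.

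**Step 1: reproduce the stated precision.** Half-width = 1.96 × √(p(1−p)/n).

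- Intervention: 1.96 × √(0.25/100) = 0.098, stated as ±0.1.
- Comparison: 1.96 × √(0.25/150) = 0.080, stated as ±0.08.

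Both match with no design effect, so the figures are those of a simple random sample.

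**Step 2: allow for clustering.** Design effect DE = 1 + (m − 1) × ICC, where m = n / number of sites. Half-width = 1.96 × √(0.25 × DE/n). The values of m are 100/4 = 25, 150/8 = 18.75 and 150/4 = 37.5.

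| Assumed ICC | Intervention, 4 sites: DE; effective n; half-width | Comparison, 8 sites: half-width | Comparison, 4 sites: half-width |
|---|---|---|---|
| 0.01 | 1.24; 81; 0.1091 | 0.0868 | 0.0935 |
| 0.02 | 1.48; 68; 0.1192 | 0.0931 | 0.1052 |
| 0.05 | 2.20; 45; 0.1454 | 0.1099 | 0.1345 |

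An unadjusted nominal 95% interval in the intervention group would then cover about 92%, 89% and 81% (2Φ(1.96/√DE) − 1). These figures use the normal quantile. With a t quantile on 4 − 1 = 3 degrees of freedom, the intervention half-widths become about 0.177, 0.194 and 0.236.

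**Step 3: sensitivity to site numbers.** The site counts are minimums. With 10 intervention sessions (an assumption), m = 10, and the half-width is 0.106 at ICC 0.02 (DE 1.18) and 0.118 at ICC 0.05 (DE 1.45).

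**Step 4: between-group test, limiting case.** If every venue lay wholly in one group, the variance of the difference would be inflated by V = (DE₁/100 + DE₂/150)/(1/100 + 1/150), and a nominal 5% test would have true size 2 × (1 − Φ(1.96/√V)). With eight comparison sites:

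- ICC 0.02: V = 1.43, size about 10%.
- ICC 0.05: V = 2.075, size about 17%.

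With four comparison sites the sizes are about 12% and 21%. The article does not guarantee the condition behind these figures, because individuals may switch group within a venue.

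**The case against.** **It is a feasibility study.** Acceptability and accessibility are the primary outcomes and are assessed qualitatively. Intention and uptake are secondary, the tests are exploratory, and no p-value threshold or go/no-go rule is set. This stands and limits the severity. It does not rescue the precision statement, which is a definite claim.

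**The sentence on individual responses may mean something else.** In context it can be read as saying that people are analysed by what they received and not by the status of their venue. A reader might infer that it rules out any adjustment. It does not: a mixed model or GEE also uses individual responses, and the tests are given only as examples. The precision figures are the firm part of the point; the analysis text is at fault for naming only methods that assume independence.

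**The 10% to 17% test sizes.** A reader might take these as the true error rates of the planned tests. The documents do not support that. Switching between groups within a venue, and virtual delivery including a recorded session, loosen the link between venue and group, so for the same ICC and site numbers the inflation should be smaller than in the limiting case.

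**Planning harm.** A reader might infer that the effect sizes carried forward are themselves biased by ignoring clustering. They are not, on that account alone, and a design effect can be added later. What is lost is any local estimate of between-venue variation to base it on. Nor does the article say that a definitive study would be allocated by venue, so that part is conditional.

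**One clinician per venue.** This cannot be assumed either: the article expects to interview 10 delivering clinicians but sets a minimum of four intervention sites.

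**Conclusion.** The point holds at moderate weight. The stated ±0.1 and ±0.08 are correct only for independent participants, and the recruitment and delivery described in the same article make independence implausible. The direction holds for the single-group intervals under any positive within-venue correlation. The size is illustrative: with four intervention and eight comparison sites, about ±0.11/±0.09 to ±0.145/±0.11 over assumed ICCs of 0.01 to 0.05, smaller with more sites and larger for comparison if there are only four sites in that group.

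Between-group tests would tend to be anti-conservative, by an amount that cannot be fixed from the documents. No conclusion about the primary outcomes is affected.

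**What to change.** 1. **Sample size paragraph.** State that ±0.1 and ±0.08 assume independent participants and p = 0.5. Add the design-effect-adjusted half-widths over a stated range of assumed ICCs and site numbers, labelled as assumptions. Settle whether the comparison sites number four or eight.
2. **Sampling approach and recruitment, and Data analysis plan (Phase 1).** Keep individual-level data, but compute intervals and any exploratory comparison allowing for clustering by recruitment venue or session, using GEE or a mixed model with a small-sample correction. A comparison of site-level proportions by t-interval is not suitable, since one site may contain both groups.
3. **Data.** Record venue or session for every participant, with a code for virtual attendance. The identifiers listed under Data validation do not include venue, so confirm whether the survey forms or session records hold it.
4. **Feasibility outputs.** Report between-venue variation or the ICC with its confidence interval, and apply a design effect when the effect sizes are used to size a definitive study delivered by venue.

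The cost is some wording, a few lines of analysis code and possibly recovery of venue from session records. The June 2023 status section lists analysis as still to come, so at that date the change was still possible. The price is wider intervals and a very imprecise ICC from so few sites; a model-based correction with about four sites per group is itself weak and should be reported as such.

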## Evaluation data collection and protocol

### Phase 1: Outcome evaluation

#### Participant surveys

Participants in the intervention and comparison groups will provide data through self-completed surveys. The survey tools included as supporting information in S2–S4 Appendices. Participant information sheets will be translated into Bengali and Urdu and will be provided to participants in the intervention and comparison groups ahead of asking them to participate. Printed copies will be made available at the participating mosques. These will be available in digital and hard copy.

Where possible, participants will be asked to complete the consent and survey forms digitally, shared via text message or email. This is to reduce the administrative burden of data entry given the limited study resources. A digital consent form will be included at the start of the baseline survey to gain participant consent. Feedback from stakeholders suggested that we host ‘drop-in’ sessions where peer-researchers are available to support participants with survey completion. We will explore this and plan accordingly with the participating venues for each of the three surveys.

Participants in the intervention and comparison groups will be asked to complete a baseline survey. A survey used in a previous study [32] has been adapted to suit the current study. Participants receiving the intervention will need to complete this before attending the information session (either face-to-face or virtually). For those attending the information sessions face-to-face, and who have not yet completed the consent and baseline survey online, paper forms will be available. Peer-researchers will be available to support participants to complete the survey. If individuals do not fill in the baseline survey, they will not be included as participants, but they will still be permitted to attend the information sessions.

Participants in the control group will be provided with the link to the online consent and baseline survey forms. This information will be available at the participating control sites for participants to request, or they will be able to sign up to participate and the link will be sent to them by text message or email. ‘Drop in’ sessions to support with survey completion at control sites will also be explored.

Intervention participants will be asked to complete a post-intervention survey ideally immediately after receiving the intervention (digitally, or paper form), otherwise within 5 days of receiving the intervention. Those attending face-to-face will have the option of completing a paper form, and if this is done immediately after the session, peer-researchers will be available to support if they need it.

Participants in both groups will be asked to complete a self-reported follow-up survey at six months, when a link to the electronic survey will be shared via email or text message. We will work with the participating mosques to share reminders with the aim of increasing the number of responses. A reminder email and text will be sent if no response is received within one week of the required deadline. The ‘drop in’ offer will also be considered.

Primary outcomes measures will be the acceptability and accessibility of the intervention for participant as well as clinicians delivering the intervention. These will be assessed via the focus groups and semi-structured interviews respectively.

Secondary outcome measures will be intention to screen and use of screening as reported by the participant. Intention to screen will be assessed by the likelihood of participation in bowel screening when invited and the likelihood of requesting a screening kit, if eligible to receive one, measured at baseline, post-intervention, and six months. Use of screening will be measured by the request of a faecal immunochemical screening kit and completion / returning of the test, if eligible for screening, as reported by the participant at six months.

#### Data validation

Participants will be asked to provide name, address, date of birth and NHS number (if known). This will enable us to validate actual screening intention/uptake through the Screening Hub records (kits requested/returned) between participants in the intervention and the comparison groups. We will carry out a validation at six months post-intervention.

### Phase 2: Process evaluation

#### Focus groups

All data collection for this phase will be conducted post-intervention and with the intervention group only. Two focus groups will be conducted with participants who have received the intervention. Each focus group will have 6–8 participants (up to 16 in total). Peer-researchers will support the delivery of the focus groups. The focus group discussion will examine experiences of the intervention, accessibility, acceptability and attitudes towards screening. The research team are from diverse ethnic backgrounds, including some Muslim researchers, and we will endeavour to be sensitive to the preferences and dynamics of participant groups when conducting fieldwork. Focus group participants will be compensated for their travel and subsistence costs. The focus groups will be single-sex [33]. We will take a gatekeeper-led and emergent approach to this. Gatekeepers will be the leaders and volunteers at the mosques who are typically responsible for organising community events and are well known and trusted members of their local communities.

#### Semi-structured interviews

We will conduct semi-structured interviews with each of the clinicians involved in the delivery of the intervention. It is anticipated that this will be with 10 individuals. The interviews will most likely be conducted remotely (although in person where possible) and will explore how the professionals became involved in the intervention, the training they received, the experiences and perceptions of delivery, and suggestions for improvements and refinements. These interviews will be one-to-one (although in pairs if requested by participants) and will last around 40 minutes.

A summary of the data management plan can be found in S2 Fig.

